**Discussion:**

MHRT was newly developed for the treatment of TS. MHRT may lead to greater reductions in tic severity than traditional HRT. Changes in the network parameters of the DMN and SN may show associations with the efficacy of MHRT.

**Clinical trial registration:**

http://www.chictr.org.cn, ChiCTR2100053077, China.

## Introduction

Tic disorders (TDs) are mainly first recognized in children and adolescents (1). They are neurodevelopmental disorders characterized by motor and/or phonic tics. TDs are graded into three categories according to clinical manifestation: transient TD, chronic TD (motor or vocal), and Tourette syndrome (TS). TS is characterized by the presence of both movements and vocalizations, which last for more than 1 year (2). TS is a common disorder in children and adolescents, with a prevalence of 1 and 3% (3), respectively. TS has been regarded as the most serious and intractable type of TD. Previous studies have estimated that ~60–80% of symptoms of TS can last beyond the age of 16, and ~23% of these individuals will be left with a moderate and severe tic that causes serious social impairments (4). The cause of TS has not yet been fully elucidated, and the treatment also lacks definitive and effective methods. Therefore, studies of the pathogenesis and therapeutics for TS show great clinical significance and need to be further developed.

At present, the treatment of TD mainly includes psychological interventions and pharmacological treatment. Medications (e.g., aripiprazole and tiapride hydrochloride) are the main form of treatment and have been relatively successful in treating symptoms. However, drug treatment has some side effects (e.g., weight gain and extrapyramidal syndrome) (5). Consequently, nondrug treatments [e.g., habit reversal training (HRT) and transcranial magnetic stimulation], especially behavior therapy (mainly HRT), have gradually attracted attention due to their safety (6).

Among many behavioral therapies for TD, the most pivotal and classic therapy is HRT. The latest guidelines from the American Academy of Neurology in 2019 also suggested HRT as the first-line treatment for TD (7). Moreover, behavior therapy has been recommended in Europe and Canada as a first-line treatment for TD (8–10). Much experimental evidence to date has shown the safety and effectiveness of behavior therapy (6, 11–13). The long-term effects of behavior therapy for tics also support guidelines recommending behavior therapy as the first-line intervention for tics (14, 15). Research on behavior therapy has implications not only for clinical practice but also for an understanding of the etiology of TD. For example, McGuire et al. found that cognitive control processes may influence the tic severity reductions observed with behavior therapy (16).

However, based on some outcome studies, the efficacy of HRT still needs to be further investigated. A randomized control trial (RCT), in a comparison trial of HRT to exposure and response prevention (ERP), had results indicating that the ERP group experienced significantly greater reductions in tic severity (17). In another comparison trial, HRT and awareness training were compared, and participants in the HRT group experienced only a minimal benefit above awareness training (18). These studies showed that awareness training is an important component of HRT. Moreover, the treatment effects are also typically affected by age. Participants under the age of 10 may have difficulty learning awareness training due to difficulty with premonitory urge recognition (19). The key step of HRT is the detection of premonitory urges (PUs) (20), but insufficient awareness may lead to decreased curative effects, especially in younger individuals. Moreover, tics may be accompanied by emotional problems, such as anxiety and depression, but traditional HRT training does not adequately resolve these emotional problems. More improvements are needed to compensate for the limitations of HRT.

Mindfulness is attention to present moment experience without judgment, primarily to become reflectively aware of the nature of emotional and cognitive patterns based on a shift of emphasis from contents (e.g., of perceptions or thoughts) to processes (21). Mindfulness training shows salutary effects on cognition (increased awareness) and emotional wellbeing (improved mood and stress relief) in children and adolescents (22–24), which addresses the two problems of HRT. Therefore, we will attempt to integrate mindfulness into HRT and call the new therapy “mindfulness-based habitual reversal training” (MHRT). Improvements in the curative effects may be mainly based on two links: the first link is that mindfulness can enhance awareness of PUs; the second link is that mindfulness can alleviate the anxiety associated with tics during relaxation training (25).

Some theoretical understandings of the brain mechanisms involved in mindfulness take their lead from considerations about the roles of the major brain networks and their interplay (21). Functional connectivity in intrinsic brain networks, which include the salience network (SN), default mode network (DMN) and central executive network (CEN), has been suggested to be important in the networks prominently involved in cognition and mindfulness (26, 27). Mindfulness training involves participants training the attention system to inhibit irrelevant sensory stimuli and enhance relevant sensory stimuli (28) and consists of focusing attention on physical sensations (29). This suggests that mindfulness can improve the patient's perception of PUs. Mindfulness-mediated decreased connectivity between the cuneus and SN may be related to self-awareness (27). The primary node of the SN is within the anterior insular cortex (30). Neuroimaging studies have suggested that PUs are associated with the insula and anterior cingulate cortex (ACC) (31, 32). A review indicated that mindfulness-based treatments may be effective in restoring connectivity between the DMN and the CEN and SN in individuals with PTSD (33). Meditation practitioners showed significantly stronger connectivity between the DMN and SN (34), as well as increased connectivity in systems important for emotion and reward (35). This may explain why mindfulness reduces anxiety and depression and enhances wellbeing. On the other hand, TS patients exhibited a reduction in serial information transfer within the DMN and SN (36). TD patients benefit from increased functional connectivity within the DMN as a compensatory function (37). From the perspective of brain networks, we speculate that mindfulness can provide useful support for conventional HRT in TS patients. To understand the underlying mechanisms of mindfulness in TS, we will focus on two key brain networks, the DMN and SN.

Therefore, this project plans to carry out an RCT of MHRT in the treatment of TS, further systematically verify its efficacy and explore the brain mechanisms underlying the synergy of MHRT. The significance and value of this study are to form a suitable psychological and behavioral intervention scheme for TS, resolve the dilemmas in clinical treatment to a certain extent, and provide data for further clarifying the pathophysiological mechanisms underlying TS.

## Methods/design

### Participants

#### Recruitment of participants

Recruitment of TS patients will be from the Department of Psychiatry, Beijing Children's Hospital, where participants will have received a diagnosis of TS from an experienced multidisciplinary team including at least two attending psychiatrists using the diagnostic criteria in the DSM-5. The inclusion criteria were as follows: (1) 7–12 years old; (2) Chinese children's Wechsler intelligence test IQ ≥ 80; (3) first onset with no previous treatment; and (4) right-handed. The exclusion criteria were as follows: (1) diagnosed with other mental disorders, apart from obsessive–compulsive disorder (OCD) or attention deficit hyperactivity disorder (ADHD); (2) diagnosed with epilepsy or other neurological diseases (including craniocerebral trauma); (3) claustrophobia; and (4) metallic foreign objects in the body. The recruitment period was predefined for one and a half years (May 2022 to Dec 2023).

Recruitment of healthy controls will be from a primary school in Beijing. The inclusion criteria were as follows: (1) aged 7–12 years; (2) IQ ≥ 80; and (3) right-handed. The exclusion criteria were as follows: (1) diagnosed with neurological or mental diseases; (2) claustrophobia; and (3) metallic foreign objects in the body.

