#### Sample size estimation

In accordance with the experimental design, three groups of participants will be included: the HRT group, MHRT group, and psychological education and supportive therapy (PST) group.

In addition, for the sample size, we use the formulas (see Supplementary Figure S1) to **calculate** the sample size (α = 0.05, 1–β = 0.8). Taking YGTSS scores as the indicator of a curative effect and based on the effect size of 0.68 calculated in a preliminary pilot test, it was calculated that at least 23 participants were needed in each group, and the drop-out rate was estimated to be 20%. Based on previous experience, 15% of MRI scans have invalid data, resulting in at least 34 subjects being required in each group (38). Therefore, 40 patients will be recruited in each group, for a total of 120 patients in this study. In addition, another 40 healthy controls will be recruited as blank controls for the behavioral and imaging research. A total of 160 participants will be included.

All evaluators will be blinded, and the treatment condition assignment will not be disclosed until after the intervention. The clinical evaluator will not be informed of which therapeutic modality the participants will receive in the evaluation process. Moreover, all dropouts must be accounted for and reported. The reasons for dropouts are mentioned. Intention-to-treat analysis was used to assess the missing data.

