### Statistical analysis

Measures will be analyzed using IBM SPSS Statistics version 22 (IBM, Armonk, NY, United States).

First, the efficacy of MHRT will be tested using repeated measures analysis of variance (ANOVA). A 3 × 3 mixed design will be used to examine the main effects of group (MHRT, HRT or PST) as a between-subjects factor and time point as a within-subjects factor, as well as interaction effects. Second, for the imaging study, we will assess connectivity between the DMN and SN and compute the average Fisher r-to-z transformed Pearson correlations of the resting-state fMRI time-series between the nodes that belong to these resting-state networks. Pearson correlations will be used to replicate earlier functional connectivity studies. For analysis of the abovementioned neuroimaging indices, we will use univariate mixed-model analyses to assess the effects of MHRT and HRT. We will use the after-training outcomes as dependent variables, the group (MHRT, HRT, PST, and HC) as the independent variable and the baseline measure of the outcome as a covariate. We will also perform these analyses correcting for age, years of education and sex.

Measurement data will be presented as the mean ± standard deviation (x ± s). The demographic and efficacy indices of the three intervention groups before and after the intervention will be compared by multifactor analysis of variance (measurement data), and repeated measures analysis of variance and paired *t*-tests will be used for comparisons between multiple groups and before and after the intervention. In addition, we regarded at least 30% changes in YGTSS scores $\left[(\frac{\mathrm{Pr}e_{\left(YGTSS\right)}-Post_{\left(YGTSS\right)}}{\mathrm{Pr}e_{\left(YGTSS\right)}}\right)\times 100\%]$ as the clinically meaningful level.

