## Discussion

This protocol describes a study assessing the efficacy of MHRT for children with TS and associated brain network mechanisms. To the best of our knowledge, this is an original intervention technology that may be valuable for the non-drug treatment of TS. The protocol was designed to investigate multiple aspects of the treatment response, not only tic severity but also the effects of MHRT, HRT and PST on psychosocial functioning and neural physiological mechanisms.

Our results may be consistent with previous studies in patients with TS that compared the effectiveness of HRT and PST in a similarly large sample of TS patients. Based on available pilot data, we predict that patients receiving MHRT or HRT may show significant and clinically meaningful reductions in tic severity compared with patients receiving PST. We speculate that augmenting HRT with mindfulness training will enhance tic severity reductions and result in stronger awareness and lower anxiety levels. The fMRI scans may show functional changes in brain networks associated with mindfulness.

Mindfulness training can improve performance in attention, working memory and cognitive control tasks (55–57). With the potential benefits of mindfulness in children with common neurodevelopmental disorders (58), more research has been conducted in recent years. In 2020, a study investigated the feasibility of a family-based mindfulness intervention in 100 attention-deficit/hyperactivity disorder (ADHD) children's families and found that the intervention group showed greater improvements in children's ADHD symptoms (59). In 2021, Muratori et al. in a 50-child sample of adolescents with ADHD and oppositional defiant disorders showed that participating in a mindfulness meditation was associated with a greater reduction in hyperactive behaviors in the school context (60). Another pilot study using mindfulness training for children aged 8–12 years with ADHD (*n* = 140) and their parents also showed promising results (61). A study in Hong Kong demonstrated the feasibility of a mindfulness program in the Chinese context (62). Accumulating evidence supports the applicability of mindfulness-based therapy for those with mental health and neurodevelopmental disorders. The theoretical basis suggests that it can also be beneficial for patients with TS.

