## Conclusion

The findings from this work will (1) provide evidence-based information on optimizing behavior therapy targeted at youth with TS. (2) The findings will shed light on the benefits of mindfulness in improving awareness and in reducing stress among children with TS. (3) The examination of brain networks will advance our understanding of the process underlying the pathogenesis of TS and how mindfulness works.

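### TS children may have ADHD or OCD but healthy controls may not, and the imaging model has no comorbidity term, so a TS-versus-control network difference is not specific to TS

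*Protocol article*

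**What the plan says.** **Eligibility (Recruitment of participants).** TS children are excluded if "diagnosed with other mental disorders, apart from obsessive–compulsive disorder (OCD) or attention deficit hyperactivity disorder (ADHD"), so ADHD and OCD are allowed. For healthy controls the rule is "The exclusion criteria were as follows: (1) diagnosed with neurological or mental diseases; (2) claustrophobia; and (3) metallic foreign objects in the body", so ADHD and OCD are absent by design.

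**Role of the controls (Sample size estimation).** "another 40 healthy controls will be recruited as blank controls for the behavioral and imaging research".

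**Imaging model (Statistical analysis).** The dependent variable is the after-training network index, with "the group (MHRT, HRT, PST, and HC) as the independent variable and the baseline measure of the outcome as a covariate". The section then adds: "We will also perform these analyses correcting for age, years of education and sex". No ADHD, OCD or CY-BOCS term and no comorbidity-free subset is named.

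**Measurements (Assessment instruments).** The Kiddie-SADS-L covers ADHD as a current or past diagnosis, and the CY-BOCS rates obsessive-compulsive severity. No ADHD severity scale is listed.

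**Intended conclusions.** The end of the Introduction promises data that clarify the pathophysiology of TS. The Conclusion says: "The examination of brain networks will advance our understanding of the process underlying the pathogenesis of TS and how mindfulness works". The section Construction of the network plans to relate network change to improvement in tics and premonitory urges.

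**The concern.** Controls are not randomised, so a TS-versus-control difference carries everything in which the two populations differ. Here one such difference is built in by the eligibility rules: some TS children have ADHD or OCD and no control does. If either condition shifts a DMN or SN index, the group factor absorbs that shift and it reads as a TS effect.

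The covariates that the article fixes do not close the gap. Age, education and sex do not measure comorbidity. The baseline outcome removes part of a stable offset, but not all of it, because a single baseline scan measures the child's stable level with error.

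A related question is one of mechanism. The Discussion cites a mindfulness trial in which "the intervention group showed greater improvements in children's ADHD symptoms". By the article's own reasoning, MHRT might change a network by way of ADHD symptoms rather than tics.

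At stake is what the control comparison and the mechanism analysis may conclude. The estimate of whether MHRT works better than HRT or PST is not at stake.

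**Working it through.** **Inputs from the article**
- 40 recruited per group; drop-out 20%; invalid MRI scans 15% (Sample size estimation).
- These two rates reproduce the article's own inflation step: 23 / 0.80 / 0.85 = 33.8, rounded up to 34.
- Applied to 40 they leave 40 × 0.80 × 0.85 = 27.2, or about 27 usable pairs of scans per group. That is 81 TS children and 27 controls, if controls are lost at the same rates (an assumption).
- Comorbidity in controls: 0, by the eligibility rule.

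**Inputs assumed, because the article gives none**
- p, share of TS children with ADHD or OCD: 0.3–0.5.
- d, stable shift in a network index from ADHD or OCD: 0.3–0.5 SD.
- ρ, correlation between the baseline and after-training index: 0.4–0.8.
- No true TS effect.

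**Formulas**
- Offset between TS and controls before adjustment: p × d.
- Residual offset after adjusting for the baseline index: p × d × (1 − ρ).
- Standard error, unadjusted: √(1/81 + 1/27) = 0.222. Baseline-adjusted: 0.222 × √(1 − ρ²).
- Rejection rate of a two-sided 5% test, with z = bias / SE: 1 − Φ(1.96 − z) + Φ(−1.96 − z).

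**Results for the planned, baseline-adjusted contrast**

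| p | d | ρ | bias (SD) | SE | z | rejection |
|---|---|---|---|---|---|---|
| 0.3 | 0.3 | 0.8 | 0.018 | 0.133 | 0.135 | 5.2% |
| 0.3 | 0.3 | 0.4 | 0.054 | 0.204 | 0.265 | 5.8% |
| 0.5 | 0.5 | 0.8 | 0.050 | 0.133 | 0.375 | 6.6% |
| 0.5 | 0.5 | 0.6 | 0.100 | 0.178 | 0.562 | 8.7% |
| 0.5 | 0.5 | 0.4 | 0.150 | 0.204 | 0.736 | 11.4% |

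**Check by simulation.** The four-group model with baseline covariate was simulated with 27 per group and 4,000 runs per setting. At p = 0.5, d = 0.5, ρ = 0.6 it gave a bias of 0.095 SD and 7.8% rejections for pooled TS versus controls. With a comorbidity indicator added, the bias was −0.002 SD and the rejection rate 5.4%. The randomised MHRT-versus-PST contrast rejected 5.1% without the indicator and 4.8% with it.

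**Association of network change with tic change.** If comorbidity alone shifts both changes by a SD, the induced correlation is p(1−p)a² / (1 + p(1−p)a²). With p = 0.3–0.5 and a = 0.3–0.5 this is 0.02–0.06. The control contrast is the larger problem.

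**The case against.** Four points can be made against the concern.

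1. **Admitting common comorbidities is legitimate.** This stands. The eligibility rule is not an error, and no exclusion is needed.

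2. **Covariates and sensitivity subsets are often left to an analysis plan, and this is a condensed article.** This stands in part. But the article does state its covariate list, and that list omits the one difference that its own eligibility rules create.

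3. **The imaging models are there to assess MHRT and HRT, and no baseline TS-versus-control test is spelled out.** This is a fair reading, and it makes the control contrast secondary. Still, controls sit in the group factor, and the Introduction and Conclusion draw on the imaging for statements about TS itself.

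4. **Baseline adjustment removes part of the offset.** This stands. A reader might work from an unadjusted contrast, where the same assumptions give 0.09–0.25 SD and about 7–20% rejections. Those figures do not describe the model in the Statistical analysis section, which adjusts for the baseline outcome.

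A reader might also infer that the efficacy comparison is biased. The documents do not support this. The three patient arms are randomised. At 40 per arm the chance difference in comorbid share has an SD of √(2p(1−p)/40) = 0.10–0.11, and the nominal error rate already allows for it.

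Finally, a reader might infer that a baseline ADHD covariate would separate ADHD improvement from tic improvement. It would not. That needs ADHD severity over time, and no such scale is listed.

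**Conclusion.** The point holds for the non-randomised TS-versus-control imaging comparison. Because of the asymmetric eligibility rules and the stated covariates, any such difference can partly reflect ADHD or OCD, and on its own does not support statements on TS pathogenesis.

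The size cannot be known from the article. Under the assumptions shown it is modest: a residual bias of about 0.02–0.15 SD and a false-positive rate of about 5–11% in place of 5%. Higher comorbidity, a larger shift or a lower retest correlation would raise it.

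The randomised contrasts among MHRT, HRT and PST remain unbiased, for tics and for network indices alike. What randomisation does not settle is whether a network change under MHRT runs through tics or through ADHD symptoms. The listed instruments cannot settle that either. This is a worthwhile improvement to the analysis wording, not a flaw that undermines the trial.

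**What to change.** In the Statistical analysis section:

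1. Repeat every TS-versus-control imaging comparison in TS children without ADHD or OCD, identified by Kiddie-SADS-L and CY-BOCS. Limit TS-specific pathogenesis statements to effects whose estimate in that subset has the same direction and similar size, and say in advance what counts as similar. The subset is the right basis because controls have no comorbidity, so only comorbidity-free TS children inform a TS-specific difference.
2. Add baseline ADHD diagnosis, and OCD diagnosis or baseline CY-BOCS, as covariates in the randomised-arm models. The purpose is precision, not removal of bias.
3. State that, without an ADHD severity measure over time, a network change under MHRT cannot be attributed to tic improvement rather than ADHD improvement.

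**Cost.** Analysis wording only, with instruments already in the trial and no extra participants. The covariates use one or two degrees of freedom. The subset comparison is less precise. With 30–50% comorbidity it keeps 81 × 0.7 = 57 to 81 × 0.5 = 40 TS children, and the unadjusted standard error against 27 controls rises from 0.222 to 0.234–0.248 SD, about 5–12%.

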#### Sample size estimation

In accordance with the experimental design, three groups of participants will be included: the HRT group, MHRT group, and psychological education and supportive therapy (PST) group.

In addition, for the sample size, we use the formulas (see Supplementary Figure S1) to **calculate** the sample size (α = 0.05, 1–β = 0.8). Taking YGTSS scores as the indicator of a curative effect and based on the effect size of 0.68 calculated in a preliminary pilot test, it was calculated that at least 23 participants were needed in each group, and the drop-out rate was estimated to be 20%. Based on previous experience, 15% of MRI scans have invalid data, resulting in at least 34 subjects being required in each group (38). Therefore, 40 patients will be recruited in each group, for a total of 120 patients in this study. In addition, another 40 healthy controls will be recruited as blank controls for the behavioral and imaging research. A total of 160 participants will be included.

All evaluators will be blinded, and the treatment condition assignment will not be disclosed until after the intervention. The clinical evaluator will not be informed of which therapeutic modality the participants will receive in the evaluation process. Moreover, all dropouts must be accounted for and reported. The reasons for dropouts are mentioned. Intention-to-treat analysis was used to assess the missing data.

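### The 23 evaluable participants per group cannot be reproduced from the stated effect size of 0.68, alpha 0.05 and power 0.80, so the stated calculation does not support the 80% power claim

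*Protocol article*

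**What the plan says.** The section on sample size estimation refers to formulas in a supplement ("we use the formulas (see Supplementary Figure S1"), which is not among the documents at hand. It prints the error rates ("sample size (α = 0.05, 1–β = 0.8"), the endpoint ("Taking YGTSS scores as the indicator of a curative effect") and the source of the effect ("based on the effect size of 0.68 calculated in a preliminary pilot test"). The result is stated thus: "it was calculated that at least 23 participants were needed in each group, and the drop-out rate was estimated to be 20" per cent. The section then allows for this dropout and for 15% invalid MRI data, arrives at 34 per group, and recruits 40 per group, 120 patients in all. Intention-to-treat is named for missing data.

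The section does not say whether the test is one- or two-sided, what kind of effect size 0.68 is, which pair of arms it was estimated for, or whether a correlation was used.

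The statistical analysis section plans a 3 × 3 mixed repeated-measures ANOVA for efficacy and names no baseline covariate for it. The imaging model does have one. The abstract defines the primary outcome as change scores on the YGTSS and other assessments.

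**The concern.** The article prints both the inputs and the output of its calculation, so the two can be compared, and they do not agree under any standard formula that uses only those inputs. The next figure, 34 per group, is built on the 23.

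What is at stake is how the result will be read. If MHRT and HRT do not differ significantly, readers will rely on the statement that the trial had 80% power. They need to know for which contrast, for what size of difference and under which analysis that holds. The text does not tell them. The Discussion links the pilot data to a comparison with PST ("Based on available pilot data, we predict that patients receiving MHRT or HRT may show significant and clinically meaningful reductions in tic severity", set against patients receiving PST) and only speculates that mindfulness adds to HRT.

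**Working it through.** **Inputs.** Effect size 0.68, alpha 0.05, power 0.80, dropout 20%, invalid MRI 15%, 40 recruited per group: all from the sample-size section. Assumed, because not stated: 0.68 is a between-group standardised difference d, and the test is two-sided. Other readings are tried below.

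**Step 1. The plan's own inflation.** 23 / 0.80 / 0.85 = 33.8, so 34. This agrees with the article. The problem is confined to the 23 and what is built on it.

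**Step 2. Two-arm comparison.** n per arm = 2(z₀.₉₇₅ + z₀.₈₀)² / d² = 2(1.960 + 0.842)² / 0.68² = 33.9, so 34. Solving with the t distribution gives 34.9, so 35.

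**Step 3. Other readings using only the printed inputs.**

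| Reading | n per group |
|---|---|
| Two-arm, one-sided (normal / t) | 27 / 28 |
| Paired or one-sample, two-sided (normal / t) | 17 / 19 |
| Three-group ANOVA, f = 0.68 | 9 |
| Three-group ANOVA, f = 0.34 (half of d) | 29 |
| Three-group ANOVA, one arm shifted by 0.68 (f = 0.32) | 33 |
| Three-group ANOVA, extremes 0.68 apart, third arm midway (f = 0.28) | 43 |
| Two-arm, Bonferroni for three pairs (normal / t) | 46 / 47 |

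None gives 23.

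**Step 4. What does give 23.** Each route needs an input that the article does not print, or changes one that it does.

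- ANCOVA on baseline: 33.9(1 − r²) = 22.9 at r = 0.57.
- Change score, with 0.68 in units of the post-score SD: 33.9 × 2(1 − r) = 23.1 at r = 0.66.
- Between-groups effect in a repeated-measures ANOVA, three groups. With f = 0.32 and three time points, n is 22, 23 and 24 at within-person correlations 0.50, 0.55 and 0.60. With f = 0.34 and two time points it is 22 at 0.50 and 23 at 0.55.
- Paired formula at 90% power: (1.960 + 1.282)² / 0.68² = 22.7. The article states 80%.

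**Step 5. Power at d = 0.68** (two-sided t test, alpha 0.05, one unadjusted pairwise contrast).

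| Evaluable per arm | Origin | Power | Difference detectable with 80% power |
|---|---|---|---|
| 23 | stated minimum | 62% | 0.84 SD |
| 32 | 40 × 0.80 | 76% | 0.71 SD |
| 40 | all randomised | 85% | 0.63 SD |

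**Step 6. Effect of adjusting for baseline.** With 32 per arm and an assumed baseline correlation of 0.5, ANCOVA works with an effective difference of 0.68 / √(1 − 0.25) = 0.785, and power is about 87%.

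**The case against.** The strongest reply is that the formula sits in a supplement that is not at hand, and that the planned analysis is a repeated-measures one. A standard repeated-measures formula with a moderate within-person correlation gives 23 (step 4). An article that leaves one correlation to its supplement has a reporting gap, and no arithmetic error has been proven.

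Part of this stands. Because the formula is unseen, the supportable statement is that 23 is not reproducible from the printed inputs. It is not established that the right number is 34 or 35. Two things limit the reply. First, the article presents 0.68, 0.05 and 0.80 as the basis of the 23; if a correlation drove the answer, the decisive input is missing from that account. Second, the repeated-measures formula that gives 23 powers the group effect averaged over all time points, baseline included, where randomised arms are not expected to differ. It does not match a change-score outcome, so it would not justify 23 even if it had been used.

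Three stronger readings are tempting and are not supported.

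- A reader might infer that the trial lacks 80% power. It recruits 40 per arm, not 23. At 0.68 the power is about 85% if all 40 are analysed, in keeping with the stated intention-to-treat principle, and falls about 4 points short only with 32 completers and no baseline adjustment.
- A reader might apply 0.68 to the roughly 27 per arm with usable scans (40 × 0.80 × 0.85 = 27.2) and quote an imaging power. The 0.68 is a YGTSS effect, the article gives none for imaging, and the imaging model already adjusts for baseline. An invalid scan also does not remove a YGTSS score.
- A reader might infer that the trial is underpowered for MHRT versus HRT. The article gives no effect size for that pair and designates no primary contrast, so only the detectable difference can be stated.

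**Conclusion.** The point holds in this form: 23 per group cannot be reproduced from an effect size of 0.68, alpha 0.05 and power 0.80, and the 34 per group inherits the problem. On the assumption of a two-sided, unadjusted two-arm comparison with 0.68 as a between-group d, the requirement is 34 to 35 evaluable per arm, and 23 gives about 62%.

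The consequence is modest because 40 are recruited: about 85% with all 40 and about 76% with 32. These figures apply to one pairwise YGTSS contrast without multiplicity adjustment. The 80% claim is thus unsupported by the calculation as stated, met if everyone is analysed, and narrowly missed among completers. Should-fix.

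**What to change.** Keep 40 per arm and rewrite the sample-size paragraph:

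- Correct the 23 and the 34, or give the formula input that produces them.
- State what kind of effect size 0.68 is, which contrast it was estimated for, whether the test is one- or two-sided, and any assumed correlation.
- Restate YGTSS power at 32 and 40 per arm (about 76% and 85% if unadjusted), with the detectable pairwise difference, explicitly including MHRT versus HRT: about 0.71 SD at 32 and 0.63 SD at 40.
- If 80% is to be claimed with 32 completers, make the YGTSS analysis baseline-adjusted and state the correlation assumed. At 0.5, power is about 87%.
- Give no imaging power based on 0.68.

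The cost is one rewritten paragraph and no additional patients. Without baseline adjustment, the stated power for completers becomes slightly less favourable. Adopting the adjustment also means amending the efficacy analysis.
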